#### Exclusion criteria

Participants will be excluded if they suffer from serious life-threatening disease, such as disease of the heart and brain, blood, vessels, liver, kidney and hematopoietic system, and psychotic patients. Participants will not be eligible if they are female and whether pregnant or lactating. The following conditions

are also excluded items: appeared a single nerve palsy, or cauda equina nerve palsy, manifested as muscle paralysis or have rectum or bladder problems; complicated with lumbar spinal canal stenosis and space-occupying lesions or for other reasons; complicated with lumbar spine tumors, infections, tuberculosis; moxibustion syncope and unwilling to be treated with moxibustion; do not sign informed consent.

### Treatment protocol

#### Heat-sensitive moxibustion

Moxibustion will be performed by certified acupuncture medical doctors at four centers. Qualified specialists of acupuncture in traditional Chinese medicine with at least five years of clinical experience will perform the acupuncture in this study. All treatment regimens will be standardized between four centers practitioners via video, hands-on training and internet workshops. Participants will be randomly assigned to the heat-sensitive moxibustion group, the conventional moxibustion group. In the former groups, a 22 mm (diameter) × 120 mm (length) moxa-sticks (Jiangxi Traditional Chinese Medicine Hospital, China) will be used. The patient is usually in the comfortable supine position for treatment, with 24°C to 30°C temperature in the room.

For the heat-sensitive moxibustion group, the moxa-sticks are lit by the therapist and held over the region consisting in two Da Changshu (BL 25) and Yao Shu (Du 2) of patients. The warming suspended moxibustion about distance of 3 cm are used to search for the acupoint heat-sensitization phenomenon. The following patient sensation will suggest the special heat-sensitization aupoint: diathermanous sensation due to moxa-heat, defined as the heat sensation conducting from the moxa local skin surface into deep tissue; expand heat sensation due to moxa-heat, defined as the heat sensation spreading to the surrounding little by little around the moxa point; transfer heat sensation due to moxa-heat, defined as the heat sensation transferring along some pathway or direction. When some acupoint exists one below sensation at least, therapists mark the point as a heat-sensitive acupoint. We try our best to seek all the special acupoints in each patient by the repeated assessment.

The therapists begin to treat patients from the most heat-sensitive intensity acupoint. Treatment sessions end when patients feel the acupoint heat-sensitization phenomenon has disappeared. Generally speaking, we select one point each time. One point is treated 45 minutes. Patients receive the treatment for two times daily in the first four days and for one time daily in remaining ten days. The full treatment contains 18 sessions over 14 days.

#### Conventional moxibustion group

Patients assigned to the conventional moxibustion group will receive fixed acupoint moxibustion. Common practices are similar with the first group. The different manipulation is that the therapists carry out warming moxibustion in traditional acupoint, selecting Da Changshu (BL 25), Wei Zhong (BL40) and A-shi Xue. One point is treated 15 minutes a time. The total time is 45 minutes as well. Three points are treated by suspended moxibustion at the same time. In the treatment, the therapists try to give patients the same intensity of the local warm sensation as the experimental group. The sensation of acupoint heat-sensitization phenomenon is not pursued and not avoided in the treatment. Patients receive the treatment for two times daily in the first four days and for one time daily in remaining ten days. The full treatment contains 18 sessions over 14 days.

### Statistical methods

#### Statistical analysis plan

We will conduct analysis on an intention to treat basis, including all randomized participants. Analyses will be conducted using 2-sided significance tests at the 5% significance level. The analysis of center effect will be used logistic regression method. The statistician conducting the analyses will remain blind to treatment group and data will only be unblinded once all data summaries and analyses are completed. All analyses will be conducted in the SAS statistical package program (ver. 9.1.3).

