### Outcome

The improvement Japanese Orthopedic Association has proposed a series of criteria to define patient response in the context of clinical trials of LDH. M-JOA scale is known as the modified edition of JOA Back Pain Evaluation Questionnaire [23]. According to these criteria, a patient with LDH is assessed including pain, the activities of daily life and work, function impairment, and special exams (Table 1). This scoring system was previously validated [23]. The degree of LDH is divided into three levels: mild: < 10, moderate: 10 to 20, severe: > 20.

**Table 1 T1:** List of M-JOA

Item	Grade/Classification	Score
Subjective symptoms		
Lumbar and leg pain	No	0
	Mild pain or occasional moderate pain	1
	Usual moderate pain or occasional severe pain	2
	Frequent or continuous severe pain	3
Numbness	No	0
	Occasional	1
	Frequent but relief may be on their own	2
	Continuous, not alleviated	3
Objective signs		
Paravertebral tenderness	No	0
	Mild	1
	Moderate	2
	Severe	3
Myodynamia	Grade V	3
	Grade IV	2
	Grade III	1
	Grade 0 to II	0
Straight let raising test	> 70°, straight leg drive up (-)	0
	> 45°, straight leg drive up (+)	1
	> 30°, straight leg drive up (+)	2
	< 30°, straight leg drive up (+)	3
Radiating pain	No	0
	Hip/thigh	1
	Shank	2
	Foot	3
Activities of daily life and work		
Stoop and lift heavy things	Normal stoop, lift weight > 3 kg	0
	Able to stoop, lift weight ≤ 3 kg	1
	Unable to stoop	2
	Serious difficulties in bending and lifting	3
Walking distance/time	Walking ≥ 1 km or 60 min	0
	Walking ≥ 500 m or 30 min	1
	Walking ≥ 100 m or 10 min	2
	Serious difficulties in walking	3
Daily time in bed(h)	< 10	0
	10 to 12	1
	12 to 16	2
	> 16	3
Ability to work	Full-time to do as before	0
	Although able to work, occasionally need a break	1
	Although able to work, usually need a break	2
	Unable to work	3

Therapeutic effect is assessed by comparing baseline and final conditions reported by the patient. This trial also records adverse effects reported by patients during treatment. The outcome measures above will be assessed before treatment, the 14 days after the last moxibustion session and 6 months after the last moxibustion session.

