To evaluate the improvement of severity, we will make use of M-JOA score and take the secondary analysis. Improvement rate = [(scores before treatment - after treatment score)/pretreatment score] × 100%. Definition are listed below: Clinically important improvement as ≥ 75%, markedly effective improvement as 50 to 75%, improved as 30 to 50% and ineffective as < 30%. The numbers in the four categories will be calculated respectively at every time point.

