### Design

A multi-center (four centers in China), randomized, subject blinded(group A and B) and assessor blinded, parallel positive controlled trial will be conducted at the affiliated Hospital of Jiangxi University of TCM in Nanchang, The first Affiliated Hospital of Anhui University of TCM in Hefei, Jiangsu TCM Hospital in Nanjing, and Shanxi TCM Hospital in Xian. The study will be sequentially conducted as follows: a recruitment period prior to randomization, a treatment period of 14 days (5 sessions per week), and a follow-up period of six months. Participants will be randomized to the heat-sensitive moxibustion group or the conventional moxibustion group by the central randomization system (Figure 1). This system is provided by China Academy of Chinese Medical Sciences, which adopted the computer telephone integration (CTI) technology to integrate computer, internet and telecom. The random number list will be assigned by interactive voice response (IVR) and interactive web response (IWR) [24]. The success of blinding will be assessed at each participant's last visit. Researchers who did not participate in the treatment and who are blinded to the allocation results will perform the outcome assessment. Patients meeting the inclusion criteria were randomly assigned in a 1:1 ratio to the two groups. We used the parallel controlled design and did not stratify by center or block within center.

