#### Outcome data

These will be summarized descriptively (mean, SD, median, minimum and maximum) at each time point by treatment group. The t-test, Mann-Whitney U and Wilcox on test were used for comparison of variables, as appropriate. When the data do not fit a normal distribution, we will consider more general tests such ANOVA and possible transformations.

All adverse events reported during the study will be included in the case report forms; the rates of adverse events will be calculated. The percentage of subjects with adverse events in each group will be calculated and compared using the chi-squared test or Fisher's exact test. The outcomes will be analyzed using linear mixed and logistic regression models that will include their respective baseline scores as covariates, subjects as a random effect and treatment conditions as fixed factors. Regression diagnostics will be used to check for normality of the measures and homogeneity of variance as appropriate.

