##### Follow-up data

The primary outcome will be the M-JOA scores. The primary analysis will compare the two groups at 14 days. A secondary analysis will compare the two groups at 6 months to assess if any differences between groups have been maintained over time.

Loss to follow-up is likely to lead to biased estimates of intervention effect. We will try to avoid bias due to attrition by carefully following up the participants in both groups. We will phone participants who do not complete questionnaires after a second reminder. We anticipate a 20% loss to follow-up in this trial, and will implement procedures to minimize loss to follow-up and patient withdrawal, and where possible we will collect information on reasons for patient withdrawal.

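### The one stated centre analysis is a logistic regression with no outcome named, and centre is not a listed term in the model for the numeric primary outcome

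*Protocol article*

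**What the plan says.** All of these statements are in the Protocol article.

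- **Centres.** Design describes "A multi-center (four centers in China), randomized, subject blinded(group A and B) and assessor blinded, parallel positive controlled trial". On allocation, it says the investigators "did not stratify by center or block within center".
- **Primary outcome.** Follow-up data: "The primary outcome will be the M-JOA scores", and "The primary analysis will compare the two groups at 14 days".
- **Scale.** Table 1 under Outcome lists ten items, each scored 0 to 3. The severity bands fit such a total: "The degree of LDH is divided into three levels: mild: < 10, moderate: 10 to 20, severe: > 20".
- **Centre analysis.** Statistical analysis plan: "The analysis of center effect will be used logistic regression method". No outcome is attached to that sentence.
- **Outcome models.** Outcome data names t-tests, rank tests, and linear mixed and logistic models. The model terms given are the baseline score, subject as a random effect, and "treatment conditions as fixed factors". Centre is not among them.
- **Categorical outcome.** Outcome also defines four bands of percentage improvement in M-JOA as a secondary analysis: "The numbers in the four categories will be calculated respectively at every time point".

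**The concern.** The article commits to a method for centre, but the method does not match the outcome on which the trial will be judged. A 14-day M-JOA total would normally be compared by a linear model, and the article itself plans one. Centre is not listed in that model. It is assigned to a logistic model whose outcome is left open and which most naturally suits the secondary improvement bands.

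Two things are at stake. First, any real difference in M-JOA level between centres remains in the residual variance of the primary comparison and costs precision. Second, nothing stated would show whether the treatment difference in M-JOA points varies by centre. That question is reasonable here: therapists search for the points and rank them on what the patient reports, and several M-JOA items are rated by an examiner.

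**Working it through.** **1. Does the stated centre method reach the primary outcome?**

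| Item | What the article fixes | Section |
|---|---|---|
| Primary outcome | numeric M-JOA total at 14 days | Follow-up data |
| Range | 10 items × 3 = 30, minimum 0 (counted, not stated) | Table 1 |
| Centre in allocation | none | Design |
| Centre in listed model terms | none (baseline, subject, treatment) | Outcome data |
| Centre in the simple tests | none; two-sample tests carry no covariate | Outcome data |
| Separate centre analysis | logistic, outcome not named | Statistical analysis plan |

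No line gives a centre term or a centre comparison in M-JOA points.

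**2. The plan's own sample size.** The Sample size section gives 126 per group at two-sided 5% and 90% power, with 20% loss: 126 / (1 − 0.20) = 157.5, rounded up to 158 per group and 316 in total. This reproduces. The 126 cannot be derived, because no difference or SD is given. Solved backwards with the normal formula for two means:

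d = √(2/126) × (1.960 + 1.282) = 0.408.

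**3. What centre in the model would gain.** Let ρ be the share of total variance that lies between centres. The article gives no value, so ρ is assumed. If 0.408 is standardised on the total SD, adding centre multiplies the SD by √(1 − ρ):

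power = Φ( 0.408 × √(126/2) / √(1 − ρ) − 1.960 ), where 0.408 × √63 = 3.24 (unrounded d).

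| ρ (assumed) | 3.24 / √(1 − ρ) | Power with centre |
|---|---|---|
| 0 | 3.24 | 90.0% |
| 0.01 | 3.26 | 90.3% |
| 0.05 | 3.33 | 91.4% |
| 0.10 | 3.42 | 92.7% |
| 0.20 | 3.62 | 95.2% |

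**4. The same question on the other basis.** If the planners' 0.408 was on the within-centre SD, leaving centre out divides the effective difference by 1/√(1 − ρ):

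power = Φ( 3.24 × √(1 − ρ) − 1.960 ).

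This gives 88.5%, 86.8% and 82.6% at ρ = 0.05, 0.10 and 0.20. The article does not say which SD was used.

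**5. Degrees of freedom.** With 2 × 126 = 252 evaluable patients, a linear model with intercept, treatment and baseline leaves 252 − 3 = 249. Four centres take 3 more, leaving 246.

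**The case against.** **Logistic regression may be intended for the categorical outcomes.** Outcome data plans logistic as well as linear mixed models, and the four improvement bands suit one. This is a fair reading and may be the intended one. The sentence does not say so, and on that reading the M-JOA score still has no stated centre analysis.

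**Logistic regression does not force a binary split.** A reader might infer that the plan will dichotomise M-JOA and lose much of its information. The document does not support this. A cumulative-logit model accepts ordered scores or the four ordered bands directly, no cut-off of M-JOA is proposed, and the logistic sentence concerns centre, not the treatment comparison. Nor does the article support any statement about the power of a test for centre heterogeneity.

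**Leaving centre out is valid.** A reader might infer that the primary estimate is biased by centre. It is not. Allocation was not stratified by centre, so the comparison without centre is unbiased over the randomisation, and its standard error already covers chance imbalance between centres. This stands in full. Simple randomisation is a legitimate design and is not criticised here.

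**Training is standardised across centres.** The article describes experienced practitioners and common training, which may keep ρ small. That limits the likely gain but does not settle the value.

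**A fuller plan may list centre.** It may, and silence alone would be no finding. Here, however, the article states a centre method and lists model terms, and the two together leave the primary outcome uncovered.

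**Conclusion.** The point holds as a mismatch between a stated method and the primary outcome. As written, centre is handled by a logistic model of unspecified outcome and is not examined on the M-JOA scale. The cost is precision and the absence of a centre or treatment-by-centre assessment there. There is no bias, and the primary test remains valid.

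The size is modest: power rises from 90% to about 91% or 93% if centre explains 5% or 10% of the variance, and to about 95% at 20%. These figures rest on an assumed variance share, on the standardised difference of 0.408 implied by 126 per group (taken on the total SD), and on the normal approximation. At a share of 1% the gain is negligible. The change is worth making because it is cheap and specific; the trial does not depend on it.

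**What to change.** Replace the sentence on centre in the Statistical analysis plan section with three statements:

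1. The linear model for 14-day M-JOA includes centre (four levels) as a fixed effect, alongside treatment and the baseline score.
2. Treatment-by-centre interaction is examined in that model as a supportive analysis, with the treatment difference and its confidence interval shown for each centre. The primary conclusion does not depend on the interaction test.
3. Logistic regression with centre is kept for the categorical improvement outcome, stating whether the four bands are modelled as ordered or as a binary response at a named cut-off.

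Amend the list of model terms under Outcome data to match.

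The cost is 3 degrees of freedom of about 249 in the primary model, and 3 more in the supportive interaction model. Each patient's centre is known, so no new data are needed, and randomisation and sample size are unchanged. The wording should be settled before treatment codes are released.

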#### Baseline data

Baseline characteristics will be shown as mean, standard deviation (SD) for continuous data including age, previous duration, and so on. The first step of analysis is to check for integrity of randomization. The unbalanced analysis in baseline characteristics will use ANCOVA.

#### Outcome data

These will be summarized descriptively (mean, SD, median, minimum and maximum) at each time point by treatment group. The t-test, Mann-Whitney U and Wilcox on test were used for comparison of variables, as appropriate. When the data do not fit a normal distribution, we will consider more general tests such ANOVA and possible transformations.

All adverse events reported during the study will be included in the case report forms; the rates of adverse events will be calculated. The percentage of subjects with adverse events in each group will be calculated and compared using the chi-squared test or Fisher's exact test. The outcomes will be analyzed using linear mixed and logistic regression models that will include their respective baseline scores as covariates, subjects as a random effect and treatment conditions as fixed factors. Regression diagnostics will be used to check for normality of the measures and homogeneity of variance as appropriate.

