## Background

Lumbar disc herniation (LDH) is one of the most common causes of nerve root pain, and become a painful, debilitating disorder in working adults [1]. In the majority of patients, experiencing their first episode of sciatica due to LDH, the symptoms recede to a non-disabling level within a period of six weeks [2].

LDH most typical symptoms are low back pain, accompanied by one or both lower extremity pain, numbness, pain, mostly by lumbosacral, buttocks, posterolateral to the lower limbs and feet, back radiation when bending, cough worse with movements. Herniated discs also often occur without symptoms, as revealed by magnetic resonance imaging studies in asymptomatic people. They are only clinically relevant when they impinge on a nerve root, causing radiculopathy [3,4].

In general, LDH is due to disc degeneration or trauma leading to nucleus, annulus fibrosis to the vertebral canal prominent, spinal cord or nerve root compression. As a result, conventional treatments including physical therapy, pain medication, anti-inflammatory drugs and surgery, are provided by physicians. Most patients with low back pain respond well to conservative therapy [5,6]. Recently, a large number of patients with LDH are turning to complementary and alternative treatments. Complementary and alternative treatments such as acupuncture are therefore attractive. Acupuncture is often used for LDH. For example, it is gaining popularity among LDH patients in the US and about 1 million consumers with musculoskeletal disorders utilize acupuncture annually [7].

Moxibustion is a traditional Chinese method that uses the heat generated by burning herbal preparations containing Artemisia vulgaris to stimulate acupoints [8]. Moxibustion has anti-inflammatory or immunomodulatory effects against chronic inflammatory conditions in humans [9,10]. Different moxibustion methods for treatment of LDH and their mechanism may be due to moxibustion can improve local blood circulation, eliminate nerve root inflammation and edema, loosen adhesions and improve protrusion and nerve root relations or the promotion of nerve injury repair [11,12]. Moreover, the heat of moxa treatment improves microcirculation in the lumbar vertebra.

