### Eligibility

#### Inclusion criteria

Eligible participants will be those previously diagnosed with moderate to severe LDH, according to the M-JOA criteria(> 10 score). Patients will be required to complete the baseline LDH diary. Written informed consent will be obtained from each participant. Participants 18 to 65 years of age will be recruited from outpatient and inpatient in four centers. Standard of diagnosis listed as follows:

① Pain occurred in lower back and radiated to the lower limb; ② Limitations of tender point; ③ Straight leg raising test and it's strengthen test are positive; ④ Skin sensation, muscle strength and tendon reflex have some changes; Changes in spinal posture; ⑤ CT suggestive of disc herniation. The above standard mainly originated from the guiding principle of clinical research on new drugs (GPCRND) [23]. Since the research involves moderate to severe LDH or severe LDH, the inclusion criteria will restrict the following conditions: According to the below LDH diagnosis standard, meanwhile, the triangle region formed with bilateral Da Changshu (BL 25)and Yao Shu (Du 2) of patients (Da Changshu- Yao Shu -contralateral Da Changshu intra-region) appear heat-sensitive points.

Participants will be instructed to stop LDH symptomatic relief medication during the run-in and treatment periods and will be provided the usual care instruction for LDH.

Figure 1 The flow diagram is intended to depict the passage of participants through this RCT.

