#### Sample size

We wished to estimate the sample size that would suffice to detect M-JOA between the heat-sensitive and conventional moxibustion groups. If we apply a two-sided 5% significance level, 90% power the calculated required sample size is approximately 126 participants in each group, according to the equations in [26]. Allowing for a 20% loss to follow up, a total of 158 participants will be required in each group, with 316 participants in total.

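### The outcome models adjust for the baseline score alone and leave further adjustment to an imbalance-triggered ANCOVA; a prespecified model that always includes disease duration would be more precise at almost no cost

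*Protocol article*

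**What the plan says.** Four parts of the protocol article bear on this point.

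- **Outcome data.** Outcomes are to be analysed with "linear mixed and logistic regression models that will include their respective baseline scores as covariates, subjects as a random effect", and treatment is a fixed factor. The same section lists t-tests and rank tests, which adjust for nothing.
- **Baseline data.** Means and SDs are to be shown for "continuous data including age, previous duration, and so on", so duration is collected. The section then checks the integrity of randomisation and assigns ANCOVA to unbalanced baseline characteristics. It names no covariates and no threshold for imbalance.
- **Background.** In most patients with a first episode of sciatica, "the symptoms recede to a non-disabling level within a period of six weeks".
- **Inclusion criteria.** "Participants 18 to 65 years of age will be recruited from outpatient and inpatient in four centers". Neither the inclusion nor the exclusion criteria limit the duration of symptoms, although the Objective section speaks of acute disease.

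The Follow-up data section makes the 14-day M-JOA comparison primary and the 6-month comparison secondary. The Design section says that randomisation was neither stratified by centre nor blocked within centre, and it mentions no other stratification factor.

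**The concern.** If symptoms usually settle within about six weeks, time since onset should carry information about the later score beyond the score at entry. A patient seen early in an episode may be about to improve anyway. One with the same M-JOA after a long course may not be. When such a predictor is left out of a linear model, its contribution stays in the residual and the confidence interval is wider than it need be.

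The triggered ANCOVA does not recover this. It adds a covariate only when the arms are seen to differ on it, whereas the precision gain comes from the covariate's relation to the outcome and is available when the arms are balanced too. It also means that the primary estimator is not settled until someone has judged which characteristics are unbalanced, and the article does not say how this ANCOVA relates to the model under Outcome data. At stake are some precision and a clearly fixed primary analysis.

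**Working it through.** **Inputs from the article (Sample size).** "If we apply a two-sided 5% significance level, 90% power the calculated required sample size is approximately 126 participants in each group". "Allowing for a 20% loss to follow up, a total of 158 participants will be required in each group, with 316 participants in total". No difference or SD is given.

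**Inputs assumed.** R² is the share of the variance left after baseline M-JOA that duration (and setting, if recorded) explains. The article does not give it; the range used is 0.02 to 0.20. The implied effect is taken in units of the SD left after baseline adjustment.

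**Step 1: reproduce the plan's figure.** 126 / (1 − 0.20) = 157.5, rounded up to 158 per arm and 316 in total. This matches.

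**Step 2: implied effect.** For two means, two-sided 5%, 90% power and 1:1 allocation:

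d = (1.960 + 1.282) × √(2/126) = 3.242 × 0.126 = 0.408, about 0.41 SD.

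**Step 3: effect of adding the covariates.** The residual SD is multiplied by √(1 − R²).

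- Power at 126 per arm = Φ(3.242/√(1 − R²) − 1.960).
- Patients per arm needed for 90% power = 126 × (1 − R²), rounded up.
- Unadjusted patients per arm that would give the same precision = 126/(1 − R²), rounded up.

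| R² (assumed) | SE multiplied by | Power at 126 per arm | n per arm for 90% power | Unadjusted n per arm of equal precision |
|---|---|---|---|---|
| 0 | 1.000 | 90.0% | 126 | 126 |
| 0.02 | 0.990 | 90.6% | 124 | 129 |
| 0.05 | 0.975 | 91.4% | 120 | 133 |
| 0.10 | 0.949 | 92.7% | 114 | 140 |
| 0.20 | 0.894 | 95.2% | 101 | 158 |

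**Step 4: is chance imbalance an additional error?** The difference between arms in a standardised covariate has SD √(2/126) = 0.126, so its 95% range is ±1.96 × 0.126 = ±0.247. An imbalance at the edge of that range shifts an estimate not adjusted for the covariate by 0.247 × √R². That is 0.055 SD at R² = 0.05 and 0.110 SD at R² = 0.20, or 14% and 27% of 0.408.

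The half-width of the 95% interval without the covariate is also 0.247 SD. With R² = 0.20 it would be 0.247 × 0.894 = 0.221 SD. Since 0.110² + 0.221² = 0.0122 + 0.0488 = 0.0610 = 0.247², the shift is exactly the part of the interval's width that adjustment would remove. It is the precision loss of Step 3 seen from another side, not a second harm.

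**The case against.** **Adjustment is already foreseen.** A reader of the Outcome data section alone might infer that duration is merely tabulated and that any chance imbalance in it must remain in the estimate. The Baseline data section does not support this: its ANCOVA sentence covers unbalanced characteristics, and duration is one that the section names. What remains is the criticism of the rule itself: it is triggered by the data and names no covariates. The article says the statistician stays blind to group, which limits steering but does not fix the model.

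**The article is a condensed document.** A fuller covariate list may exist in an analysis plan that is not shown, and a model adjusted for baseline is not an error. Both statements are fair. But the article does state a covariate set and an imbalance-triggered rule, so the point concerns what it fixes, not what it leaves out.

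**The premise is inferred.** A reader might conclude that duration and care setting drive recovery. No section shows this. The six-week statement describes the natural course of first episodes, not an association between duration at entry and later M-JOA given baseline M-JOA. For duration the inference is plausible. For setting it is weaker: the inpatient share is not given, and the article does not say that setting is recorded as a variable. Two Table 1 items that may depend on setting, time in bed and ability to work (6 of 30 points), are part of the baseline score already in the model.

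**There is no bias.** A reader might take a chance imbalance to bias the result. Under 1:1 randomisation the baseline-adjusted linear estimate is unbiased on average, and its standard error already covers such imbalance, as Step 4 shows. This objection stands in full.

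**Conclusion.** The point holds as one of efficiency and of fixing the model in advance. The planned models carry only the baseline score, and the route to further adjustment depends on observed imbalance. Always including duration would normally be more precise and would settle the estimator beforehand.

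The size is uncertain. For R² of 0.02 to 0.20, power at 126 per arm rises from 90% to between 90.6% and 95.2%, which corresponds to 2 to 25 fewer evaluable patients per arm for the same 90%. At the low end the gain is negligible. The figures rest on the assumed R² and on an effect of about 0.41 SD back-calculated from 126 per arm. They apply to the linear model for the M-JOA score.

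No stated figure is wrong: 158 per arm follows from 126 and a 20% loss, and the trial keeps its planned 90% power without the change. This is an inexpensive improvement, not a threat to validity.

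**What to change.** Replace the imbalance-triggered ANCOVA under Baseline data with one sentence under Outcome data. It should say that the linear model for M-JOA, for both the primary 14-day and the secondary 6-month comparison, includes treatment, baseline M-JOA and previous duration (log scale), whether or not the arms look balanced. Add inpatient or outpatient status at entry if it is recorded. The case rests mainly on duration; setting is optional. Baseline characteristics can still be tabulated by arm, but the table should not decide the model.

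The cost is that one sentence and one or two degrees of freedom. Duration is already collected, and the sample size does not change.
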